### Retention strategies

Treatment retention will be defined as completing 75% of mobile mindfulness training modules. Retention rates will be ensured by: (i) emphasizing the importance of follow-up at study initiation and through follow-up; (ii) requesting three referrals at study initiation who can update a participants’ contact information; (iii) paying $10 for the end of treatment survey, $20 each for surveys at 3- and 6-months follow-up, and $0.50 per experience sampling "check-in" [24]; and (iv) paying for participation (up to $116 total) at 6-months follow-up. All randomized participants will be followed up and their true smoking status used in the analysis, and follow-up will be collected blind to group allocation [30].

### Sample size

The sample size was determined based on the prior study of in-person mindfulness training for smoking cessation [14]. Cell size was determined by a *χ*^*2*^ power analysis using one-week point prevalence abstinence at end of treatment and at 4-months follow-up from that study. Point prevalence abstinence differed between groups by 20% or more at each time point. Thus it is estimated that group sizes of 59 per group will achieve 80% power to detect a 20% group difference at *p* < .05 using a two-sided *Z*-test with pooled variance. 140 subjects will be recruited to allow for 12-15% attrition. Further, a sample size of 33 was sufficient to detect a significant prediction of smoking by craving at baseline and significant effects of meditation on smoking at end of treatment [15], therefore these group sizes will be sufficient to detect similar changes.

### Intervention and comparator

#### Intervention group

The intervention group will receive a smartphone app, Craving to Quit (www.cravingtoquit.com) which delivers mindfulness training and experience sampling daily for 22 days. An introductory email will explain that the app will help participants self-monitor their smoking habits, recognize when and how often they smoke, identify triggers for smoking, and learn methods to become more mindful of cravings and ‘ride them out’. Upon downloading the app, participants will input the number of cigarettes smoked per day and set a quit date of 3 weeks from today. They will view a tutorial explaining the app features and begin the first day.

Mobile mindfulness training is comprised of 22 modules, 5–15 minutes each, designed to teach mindfulness for smoking cessation using audio, video, animations, and *in vivo* exercises (Table 1). Participants have access to only one new module per day; subsequent days are locked to prevent skipping ahead. Four bonus modules become available across the study to bolster training. Overall the concept of mindfulness –paying attention to and accepting momentary experience –will be taught. Participants will learn three standard meditation practices: body scan, loving kindness, and breath awareness [31]. Body scan is practiced by bringing awareness to different parts of the body, and is considered to foster awareness of body sensations that constitute cravings and affective states. Loving kindness is practiced by directed well-wishing by repeating phrases such as "may X be happy,” and is considered to foster acceptance of oneself and others. Breath awareness is practiced by paying attention to the breath wherever one feels it most strongly in the body, and is considered to help retrain the mind away from habitually engaging in self-related thinking toward a more present-centered awareness.

**Table 1 Tab1:** **Mobile mindfulness training for smoking cessation modules and bonus module contents**

**Module**	**Contents**
1	Introduces the Craving to Quit program and mindfulness, introduces habit formation using an animation, and provides a guided mindful smoking exercise.
2	Setting personalized goals, e.g., list three reasons why you want to quit smoking, and provides a mindful smoking exercise.
3	Teaches body scan meditation, provides a guided body scan exercise, and provides a mindful smoking exercise.
4	Teaches how to work with cues, affective states, and craving using RAIN, and provides a RAIN exercise.
5	Introduces the concept of craving using an animation with the metaphor of craving as a tantrum toddler, i.e., let the toddler cry it out, and provides a RAIN exercise.
6	Teaches how to recognize triggers, e.g., list some of your triggers, and provides a RAIN exercise.
7	Expands on the concept of craving using an animation with the metaphor of craving as a fire, i.e., let the fire burn out, and provides a RAIN exercise.
8	Teaches how to use noting practice, i.e., the “N” of RAIN, in everyday life, and provides a noting practice exercise.
9	Teaches strategies for staying on track, and provides a noting exercise.
10	(Un)resistance Training, and provides a noting exercise.
11	Builds on noting practice by teaching curiosity, a core element of mindfulness, and provides a curiosity exercise.
12	Expands on the concept of craving and curiosity using an animation with the metaphor of a hot coal, asks “What do you get from smoking mindfully today?”
13	Teaches loving kindness meditation, provides a loving kindness exercise, and provides “Wild Geese” by Mary Oliver.
14	Teaches evaluating the costs & benefits of smoking, provides a loving kindness exercise.
15	Misperceptions about Quitting, tell a smoking buddy you are quitting today
16	Builds on noting and curiosity by teaching noting while walking meditation, provides a walking noting practice.
17	Teaches open awareness of thoughts, to work mindfully with thoughts that trigger smoking, using animations such as “Thoughts like a Radio.”
18	Builds on walking while noting with animations such as “Tripping on Thoughts,” “Autobiography in 5 short chapters” by Portia Nelson, provides a noting exercise.
19	Asks subjects to reflect on their own experience with treatment to gather evidence for how treatment helps with smoking cessation, noting practice with a particular eye out for doubt.
20	Provides tips on staying motivated and maintaining mindfulness practice, subjects write down a mantra to use and set mantra reminder.
21	Quit day ceremony, subjects tell a friend or family member that today is their quit day.
22	Incorporates mindfulness practices as a new, healthy habit, and instructs the user on which modules to return to if they relapse.
Bonus	“Big Mind Meditation” audio by Joseph Goldstein; Tree Analogy for reinforcing noting video; Attitude is Everything video; “Mountain Meditation” audio by Joseph Goldstein; Sitting Meditation audio

Participants will also be taught an informal mindfulness practice to work mindfully with cravings: Recognize, Accept, Investigate, and Note (“RAIN”) what cravings feel like as they arise and pass away. RAIN is accessible from the home page of the app so that participants may use it any time they have a craving to smoke by choosing the “Want-O-Meter.” They are directed to identify their smoking trigger, rate their craving, and choose between using RAIN to ride out their craving, or completing an audio-guided exercise to ‘smoke mindfully’ by paying attention to the moment-to-moment experience and bodily sensations of smoking.

Social support has been shown to boost quit rates [32], therefore the app is also paired with a closed online community, built on the Ning platform (www.ning.com). Features include: (1) video tutorials of how to use the app; (2) quit buddy sign ups, for individuals to go through the process with a peer; (3) forums for posting questions and insights; (4) a “Tip of the week;” and (5) an “Ask the Doc” feature to get answers from an “expert” (JB). Participants can access the community beyond their quit date in order to encourage others to quit and to bolster their own abstinence.

Additional app features include: (i) “Activity Feed” tracks interaction with the app and can be shared on the community; (ii) “My Morning Stats” tracks daily smoking to encourage a gradual taper, and daily and monthly financial savings; (iii) “Night Reflection” to reflect on daily smoking, with links to journal on the community and practice an audio-guided body scan or loving kindness meditation; (iv) “Reminders Settings” to adjust times/days to receive reminders including “Morning Stats Motivator,” “Goal Reminder,” “Check-ins,” and “Night Reflection;” (v) “My Quit Pact” which can be personalized across the intervention and includes quit date, money saved, reasons for quitting, triggers to watch for, and a personalized mantra; and (vi) “Tracker,” to track cigarettes smoked.

Experience sampling is embedded in the app as “check-ins.” Based on previous experience sampling methods for smoking cessation [33], participants will be prompted six times per day to check-in, each day of the 22-day program. They will set the daily start and end times for check-ins, their day will be divided into six intervals, and they will be prompted to check-in at a random time in each interval [23]. Each check-in will ask the following questions adapted from the Day Reconstruction Method [34] and from prior studies using experience sampling [23,24]: (1) When you started this check-in, what were you doing? Categorical response (traveling, working, eating, internet/texting, relaxing, reading, talking, grooming, housework, watching TV, shopping/errands, caring for children, preparing food/eating, exercising, other). (2) When you started this check-in, how aware were you of what you were doing? Visual analog scale (VAS) from not at all to very much. (3) When you started this check-in, how distracted or focused were you? VAS from very distracted to very focused. (4) When you started this check-in, how was your experience feeling? VAS from very unpleasant to very pleasant. (5) When you started this check-in, how were you relating to your experience? VAS from really wanted it to stop to really wanted it to continue. (6) When you started this check-in, how much were you craving a cigarette? VAS from not at all to very much. (7) When you started this check-in, how much were you feeling these emotions? VAS from not at all to extremely, for each: relaxed, anxious, joyful, tired, content, sad, excited, irritable. (8) The tracker says you have smoked (#) cigarettes today. Adjust your tracker below if needed. Today I have smoked: (#). Participants will be sent a reminder text message if their response rate drops below 3 check-ins in 24 hours. Any day with less than 3 completed check-ins will be excluded from the analysis. Based on prior studies [23] a response rate of 80% is expected.

Upon completion of the 22-day program, participants will receive an email of congratulations, reminding them that they will be paid for the check-ins they completed across the program 6-months from when they started the study, and that they will receive the next survey 1-month from when they started the study (the dates will be provided as a reminder). Links to the online follow-up surveys will be emailed to participants at 1-, 3-, and 6-months. At 6-months follow-up, participants who report one-week abstinence from smoking will take part in carbon monoxide (CO) monitoring. CO levels will be measured using piCO+ Smokerlyzer breath CO-monitors (www.bedfont.com). CO-monitors will be shipped to participants with usage instructions, and they will set up a recorded, smartphone-based video call with a researcher, during which they will use the CO-monitor and show the output to the researcher [35]. They will be provided a paid shipping return label and will be asked to return the CO-monitor in its original packaging. Once a participant has completed the 6-months follow-up survey and returned the CO-monitor (if applicable), they will be emailed an Amazon (www.amazon.com) gift card with their study payment.

#### Control group

The control group will receive experience sampling-only, to control for: (i) expectancy effects of treatment for smoking; (ii) non-specific effects of using a smartphone for smoking cessation; and (iii) potential effects of experience sampling for smoking cessation. Experience sampling may bring awareness to craving and smoking, and is similar to other interventions that teach individuals to identify triggers and track the number of cigarettes they smoke. Experience sampling-only will be delivered by smartphone app for 22 days. An introductory email will explain that the app will help individuals self-monitor their smoking habits, recognize when and how often the smoke, and identify triggers for smoking. Upon downloading the app, participants will input the number of cigarettes smoked per day and set a quit date of 3 weeks from today. They will view a tutorial explaining the app features and begin the first day. Across treatment, experience sampling procedures will be matched to the intervention group. From day 22, all study procedures will be matched to the intervention group. In addition, along with study payment at 6-months, this group will receive a free download code for the treatment app.

### Measurements

#### Primary outcome measure

The primary outcome is one-week point-prevalence abstinence from tobacco smoking at 6-months, verified by carbon monoxide monitoring [36,37] with the interviewers blinded to treatment allocation. Abstinence rates will be compared between groups using *χ*^*2*^ tests. This trial will use an intention-to-treat approach [30].

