## Methods/Design

A pragmatic RCT funded by the American Heart Association will be conducted. Participants will be allocated to either the control (experience sampling-only) or intervention (mobile mindfulness training plus experience sampling) group by basic randomization, using Yale Qualtrics Survey Tool (http://www.qualtrics.com/). Ethical approval for the procedures of this trial was obtained from the Yale University Institutional Review Board Human Investigation Committee (HIC #1301011337).

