### Recruitment and randomization

All study procedures will be automated using Yale Qualtrics Survey Tool. The study website links to a short screening survey. The survey notifies an individual if they are eligible or not eligible. If eligible, they are asked for their contact information and directed to an online consent form, which includes study contact information to ask questions. Those who provide consent are sent an email with a link to the baseline survey and a copy of the consent form. This email also includes a recommendation for nicotine replacement therapy or other pharmacotherapies [19]. At the end of the baseline survey, participants are randomized to treatment group and emailed a link to download their app and begin the study.

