#### Exploratory outcomes

Theory-based potential mechanisms will be tested using mediation analyses of variables related to smoking, craving, mood and mindfulness, and other psychological variables, evaluated using 15-minute online surveys at baseline, 1-, 3-, and 6-months from treatment initiation, including: (i) smoking demographics, including self report of smoking abstinence over the follow-up period allowing up to five cigarettes total [30]; (ii) 4-item Alcohol Use Disorders Identification Test (AUDIT-C; [38]); (iii) 15-item Minnesota Nicotine Withdrawal Scale-revised (MNWS-R; [39]) to evaluate nicotine withdrawal symptoms (i.e., craving, irritability, anxiety, depression, difficulty concentrating, appetite, insomnia, restlessness, impatience, constipation, dizziness, coughing, dreaming/nightmares, nausea, sore throat); (iv) 4-item Perceived Stress Scale (PSS; [40]) to measure the degree to which situations in one's life are appraised as stressful over the last week; (v) 12-item Smoking Self Efficacy Questionnaire (SEQ; [41]) to evaluate the self-efficacy to resist the urge to smoke; (vi) 24-item Five Facet Mindfulness Questionnaire short form (FFMQ-SF; [42,43]) to measure mindfulness related to observing, describing, acting with awareness, non-judging of inner experience, and non-reactivity to inner experience; (vii) 12-item Self Compassion Scale short form (SCS-SF; [44,45]) to evaluate how one typically acts toward oneself in difficult times; (viii) 22-item Craving Experience Questionnaire (CEQ; [46]) to measure desire and craving to smoke; (ix) exercise, eating, and relaxation methods questions, including prior meditation experiences; and (x) 6-item Gratitude Questionnaire (GQ-6;500 [47]) to evaluate one's proneness to experience gratitude in everyday life. Participants will be paid $10 for the 1-month survey, and $20 for each 3- and 6-months survey, the total to be paid at 6-months.

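### The primary χ² test is valid but leaves pre-allocation baseline predictors unused; adjusting for one or two of them would add a modest amount of power

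*Protocol article*

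**What the plan says.** Under Primary outcome measure, the article names the test: "Abstinence rates will be compared between groups using" χ² tests. It adds "This trial will use an intention-to-treat approach". No covariate or stratum appears there. Methods/Design says that allocation is "by basic randomization, using Yale Qualtrics Survey Tool"; no blocks or strata are mentioned.

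Recruitment and randomization gives the order of events: "At the end of the baseline survey, participants are randomized to treatment group". Baseline answers therefore exist before anyone is allocated. Exploratory outcomes lists what those surveys contain, including smoking demographics, craving, withdrawal and a "12-item Smoking Self Efficacy Questionnaire", all "evaluated using 15-minute online surveys at baseline, 1-, 3-, and 6-months from treatment initiation". That section uses them for mediation analyses.

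Sample size rests on the same unadjusted comparison: "it is estimated that group sizes of 59 per group will achieve 80% power to detect a 20% group difference", two-sided at 0.05, by a Z-test with pooled variance. The recruitment target is 140.

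**The concern.** With about 70 people per arm and a binary outcome, a baseline variable that predicts quitting carries information that a two-by-two table cannot use. Leaving it out costs some power. It also leaves the investigators without a prespecified response if the arms turn out to differ on a variable that matters, and an adjustment chosen after seeing that difference is open to dispute.

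This is a question about a method the article commits to, not about a detail it omits. What is at stake is efficiency and the standing of any later adjusted result, not the validity of the primary test.

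**Working it through.** **1. The plan's own figure.** The pooled formula is n per arm = [1.96·√(2p̄(1−p̄)) + 0.8416·√(p₁(1−p₁) + p₂(1−p₂))]² / 0.2². At 10% vs 30% this is (1.96×0.5657 + 0.8416×0.5477)² / 0.04 = 61.6, so 62. It gives 57 at 8% vs 28%, 60 at 9% vs 29% and 82 at 20% vs 40%. The stated 59 therefore fits a control rate of about 8–9%. (The unpooled formula at 10% vs 30% also gives 58.9, so 59.) The article states no control rate for the design. Its Background gives 20–30% abstinence at 6–12 months for behavioural treatments, so both the low range and 20% are examined. The attrition step is sound: 118/0.85 = 138.8, so 139, against 140 recruited. At 70 per arm the pooled formula gives power 0.849 at 10% vs 30% and 0.738 at 20% vs 40%.

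**2. Is the unadjusted test valid?** Simulation used simple randomisation of 140 and 4,000 replicates per setting. Null rates were 8% and 20%, with log-odds slopes per SD of 0, 0.4, 0.8 and 1.2. The unadjusted test rejected in 0.046–0.059 of replicates (Monte Carlo SE about 0.003), near 5% whatever the strength of the predictor.

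**3. How large is a chance imbalance?** The standardised mean difference of one covariate has SD √(2/70) = 0.169. P(|difference| > 0.25) = 2[1 − Φ(0.25/0.169)] = 0.139.

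Given an imbalance of 0.25 SD and no treatment effect, the risk difference shifts by about ln(OR) × 0.25 × (average of risk × (1 − risk)). At 10% abstinence and OR 1.65, p(1−p) serves as an upper bound for that average: 0.501 × 0.25 × 0.09 = 0.011. At 20% and OR 2.7, the average over the score is about 0.139: 0.993 × 0.25 × 0.139 = 0.034. The range is about 1–2 points at 10% and 2–3 points at 20%. By normal approximation, the false-positive chance given that imbalance is about 5.5–8%.

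**4. What does adjustment gain?** The adjusted test is a logistic likelihood-ratio test with one baseline score, N = 140. Odds ratios are exp(slope).

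| Rates | OR per SD | Unadjusted | Adjusted |
|---|---|---|---|
| 8% vs 28% | 1.49 | 0.895 | 0.901 |
| 8% vs 28% | 2.23 | 0.889 | 0.916 |
| 8% vs 28% | 3.32 | 0.886 | 0.932 |
| 20% vs 40% | 1.49 | 0.741 | 0.758 |
| 20% vs 40% | 2.23 | 0.747 | 0.786 |
| 20% vs 40% | 3.32 | 0.750 | 0.838 |

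With two covariates in the model, one of them prognostic at OR 1.65, 2.2 or 2.7, the gain is about 1–4 points at 10% vs 30%. At 20% vs 40% it is about 3–6 points, from 0.73–0.75 to 0.76–0.81.

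**5. What does it cost?** Expected quitters are 70×0.10 + 70×0.30 = 28, or 70×0.08 + 70×0.28 = 25.2. Adjusted type I error was 0.050–0.068 with one covariate and about 0.052–0.065 with two, against 0.046–0.060 unadjusted. With a useless covariate (slope 0), adjusted power at 8% vs 28% was 0.892 against 0.888, so a looser test explains little of the gain.

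**6. Arm sizes.** Under simple randomisation of 140, P(arms differ by 20 or more) = 0.108. A 60/80 split lowers power from 0.877 to 0.865 at 8% vs 28% and from 0.738 to 0.723 at 20% vs 40%.

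**The case against.** The strongest reply is that nothing here is an error. The test matches the sample-size calculation, adjustment is often settled in an analysis plan that is not shown, and the article does not exclude a supporting adjusted analysis. No passage says that any baseline variable predicts quitting, so the gain rests on assumed odds ratios, and at the low control rates power already exceeds 80%. All of this stands, and it keeps the point modest. It does not remove it, because the article names the primary test and a better-informed one is available from data already collected.

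Four stronger readings are tempting, and the documents do not support them.

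- *That the χ² comparison is biased.* Under randomisation it is not. Imbalance matters only conditionally, once observed.
- *That the app entry supplies a baseline covariate.* Under Intervention group, "participants will input the number of cigarettes smoked per day" on downloading the app, and the download link is sent after randomisation. That value is post-allocation. Cigarettes per day should come from the earlier smoking questions. Exploratory outcomes does not itemise it, but eligibility requires at least 5 per day, so it is evidently asked before allocation.
- *That simple randomisation puts 59 per group out of reach.* If 119 remain after 15% loss (140 × 0.85), there is an 85% chance that one arm is below 59. That is because only a 59/60 split passes. With exactly 70/70 allocated and independent 15% loss in each arm, the chance is still 59%. The cause is mainly the thin margin of 119 over 118.
- *That blocking is needed.* Unequal arm sizes cost only about one point of power.

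**Conclusion.** The point holds as an efficiency improvement to a stated method, not as a flaw that threatens the trial. The χ² test keeps its error rate. Prespecified adjustment would make it more likely that a true effect is detected and would settle in advance how a visible imbalance is handled.

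The benefit matters most if control abstinence is nearer 20%, where unadjusted power falls short of the planned 80%. A gain of about 9 points (0.750 to 0.838) appears only with a strong predictor, at an odds ratio of 3.32 per SD. All gains assume that the chosen variable is prognostic, that all 140 are analysed and that allocation is simple, which is the natural reading of the article's wording but is not spelled out.

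**What to change.** Prespecify as the primary analysis a logistic regression of CO-verified abstinence on group, adjusted for at most two covariates recorded before allocation: baseline smoking self-efficacy, and cigarettes per day from the pre-allocation smoking questions. Report a standardised risk difference with a 95% confidence interval, which stays on the scale of the 20% difference used for the sample size. Keep the χ² test as a supporting analysis. State the covariates and their coding before any outcome data are seen.

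The cost is wording and a slightly more complex analysis. Because only about 25–28 quitters are expected at the low control rates, type I error may run slightly above 5%, so the limit of two covariates should be firm. Permuted blocks in the survey tool are optional.
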